##### Assessment of the global program by the participant

Each participant provides feedback on the global program using a five-class semi-quantitative ordinal scale (very satisfied, somewhat satisfied, neutral, somewhat unsatisfied and very unsatisfied). A questionnaire is sent to the participants 6, 12 and 24 months after the end of the global program in order to evaluate general satisfaction with the program, with the physical exercises, with the messages and information provided, with general program organization and with the program’s impact on health.

##### Assessment of the operational model

Each participant among the thirty or so recruited for this portion of the study will relate his experience of the program during the individual interviews. The experience of the occupational health physicians and of the physiotherapists will also be collected through discussion groups. The program’s elements of satisfaction/dissatisfaction as well as feasibility/acceptability will be studied using the thematic analysis of the content of these interviews and discussion groups.

**Table 1 T1:** Management of protocol violations

**Type of protocol violation**	**Definition**
1. Erroneous inclusions	
2. Poor compliance with the global program sessions	Only one absence, to either session 3 or session 4 of the training program, is tolerated from among the 6 sessions of the global program. In other cases, participants are invited to make up the sessions with another group, in order to limit “program withdrawals.” In the case of an incomplete program, the participants in the intervention group are considered to be non-compliant and deviating from the protocol.
3. Non-attendance at follow-up visits	Participants who do not attend the annual checkups with the occupational health physician of their workplace or the final physiotherapy assessment are first reminded by mail, then by telephone if necessary. It is important to have access to main criterion data for all participants in order to proceed to intention-to-treat analysis.
4. Early withdrawal	This can take place by decision of the participant or following the occurrence of an adverse event that calls into question his participation in the study. Withdrawn participants are not replaced.
5. Missing data concerning the primary outcome (sick leave related to low back pain episode)	These participants cannot be taken into account in the analysis of data.

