### Randomization

Following the inclusion visit, the study group of the participants was decided by random allocation. The randomization was stratified and balanced by blocks between the participating occupational health services. The randomization lists were computed using SAS® statistical analysis software (Version 9.1, SAS Institute Inc., Cary, NC).

Each participant was informed by mail of his assignment to a study group following an entry checkup performed by a physiotherapist. In this letter, the study group was identified and, where appropriate, the timetable for the five global prevention program sessions was included. In order to ensure the objectivity of the evaluations, the occupational health physicians were not informed as to which study group each participant was assigned (single blind). At the time of enrollment, participants were also asked not to reveal their study group to the occupational health physician.

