#### Follow-up visits

All of the participants were followed for two years: either for the two years following the beginning of the global program for those in the intervention group, or for the two years following randomization for those in the control group. This monitoring was provided by the occupational health physician in the participant’s workplace (one appointment after 12 months and the other after 24 months) and by a physiotherapist from the Centre Médico-Chirurgical et de Réadaptation des Massues – Croix Rouge Française (one appointment after 18 months).

During the 12-month follow-up visit, the intervention group members participating in the evaluation of the operational model of the PRESLO study underwent a semi-structured interview with a member of the research team, immediately following the evaluation by the occupational health physician.

Participants’ presence at follow-up visits and sessions is continually verified using the attendance sheets transmitted by the physiotherapists. Participants who miss an assessment or an appointment are reminded by the Clinical Research Assistant from the data coordinating center concerning their participation in the study or questioned regarding their reasons for absence.

Outcomes

Primary outcome

Percentage of participants with at least one recurrence of low back pain in the two years following the end of the global program.

Secondary outcomes

1. Average time to recurrence of low back pain during the study period.

2. Percentage of participants with a sick leave related to a chronic low back pain (pain for more than three months) in the two years following the end of the global program.

3. Evaluation of the compliance of the participants in the global program.

4. Feedback from the participants in the global program.

5. Feedback from the health care professionals providing the program (physiotherapists and occupational health physicians).

A recurrence is defined as a new episode of low back pain leading to a sick leave. The occupational health physicians of each workplace have access to the date and duration of the work interruptions declared for each participant and can learn the motives from the participant at the annual checkups. The collection of information regarding low back pain recurrence will therefore be comprehensive.

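### Holding the intervention-only program interviews straight after the blinded occupational physician's 12-month evaluation can reveal the arm of about thirty participants before their 24-month assessment

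*Protocol article*

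**What the plan says.** Three parts of the protocol article bear on this point.

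- **Follow-up visits** fixes who is interviewed and when. At the 12-month visit, "the intervention group members participating in the evaluation of the operational model of the PRESLO study underwent a semi-structured interview", and this took place "with a member of the research team, immediately following the evaluation by the occupational health physician". The physician's visits are "one appointment after 12 months and the other after 24 months". On the reasons for sick leave, the same section says that the physicians "can learn the motives from the participant at the annual checkups".
- **Assessment of the operational model** gives the number and the topic: "Each participant among the thirty or so recruited for this portion of the study will relate his experience of the program during the individual interviews".
- **Randomization** sets up the blind. For the sake of objective evaluation, "the occupational health physicians were not informed as to which study group each participant was assigned (single blind"). In addition, "participants were also asked not to reveal their study group to the occupational health physician".

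A recurrence is a new low back pain episode that leads to sick leave (Follow-up visits, outcomes). Dates and durations come from declared work interruptions. The cause, which decides whether an absence counts, comes from the conversation with the physician.

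**The concern.** Two stated procedures work against each other. One asks participants to hide their arm from the occupational physician. The other attaches to that physician's own visit a procedure that no control can have. A physician who sees or hears that a participant goes on to a program interview knows that the participant is in the intervention arm. The article describes nothing that would keep the interview from the physician.

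The same physician sees the participant again at 24 months and learns the motives of the second-year sick leaves. The primary outcome, the time to recurrence and the sick leave for chronic low back pain all depend on those motives. Any influence of knowing the arm could act in the intervention arm only, because no control is interviewed. Its direction is unknown.

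This route is separate from anything the physician may ask about treatment. It follows from the scheduling alone, and rescheduling removes it.

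**Working it through.** **Inputs**

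- Interviewed: about 30 (Assessment of the operational model). I take 25 to 35 as the range; that range is an assumption.
- Arm size: 650 / 2 = 325 (Number of subjects required, equal groups).
- Planned rates: 45% in controls and a 25% reduction, read as relative. This gives 0.45 × 0.75 = 33.75%, a difference of 45 − 33.75 = 11.25 points.
- Share of first recurrences that fall in year 2: not given in the article. I assume 30 to 50%, with 100% as an extreme.

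**The plan's own figure.** Two-sided 5% level, 80% power, 45% against 33.75%:

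n = [1.96 × √(2 × 0.39375 × 0.60625) + 0.842 × √(0.45 × 0.55 + 0.3375 × 0.6625)]² / 0.1125² = 295 per group.

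With continuity correction this becomes 313, which agrees with the stated 310 to within about 1%. The relative reading of the reduction is therefore the right one. The sample size is not in dispute and serves only as a yardstick.

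**Reach**

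- 30 / 325 = 9.2% of the intervention arm (25 to 35: 7.7 to 10.8%).
- 30 / 650 = 4.6% of all participants (3.8 to 5.4%).
- Controls: none.
- Not interviewed in the intervention arm: 325 − 30 = 295. The absence of an interview therefore says almost nothing about the arm.

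**Which data are exposed.** The interview comes after the 12-month evaluation, so what the physician recorded there precedes it. A participant with a recurrence recorded by then already has the primary outcome, and nothing later changes it. Only first recurrences in year 2 among interviewees are open to influence.

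**Size if true recurrences were missed**

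- First recurrences expected among 30 people over two years: 30 × 0.3375 = 10.1.
- In year 2, at 30 to 50%: 10.125 × 0.30 = 3.0 to 10.125 × 0.50 = 5.1.
- If every one were misattributed: 3.0375 / 325 = 0.9 points to 5.0625 / 325 = 1.6 points.
- Relative to the planned difference: 0.93 / 11.25 = 8% to 1.56 / 11.25 = 14%.
- With 25 to 35 interviewed: 25 × 0.3375 × 0.30 / 325 = 0.8 points to 35 × 0.3375 × 0.50 / 325 = 1.8 points.
- Extreme, with all first recurrences in year 2: 10.125 / 325 = 3.1 points.

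These are ceilings for missed recurrences, not estimates, because they take every exposed event as wrongly classified. They do not bound the opposite error, in which leave for another cause is counted as low back pain. The documents give no figure for that.

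**The case against.** The strongest reply is that a leak is possible but not shown. The interviewer belongs to the research team, the evaluation is finished before the interview starts, and participants have been asked not to disclose their arm. Nothing says that the physician arranges, sees or is told of the interview, and a journal article may well leave such arrangements to the full protocol. This stands. A reader might infer that the physicians are in fact unmasked; the documents support only that the timing can unmask them.

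A second reply is that the path to the outcome is weak. Leave dates are administrative, the motive comes from a participant who already knows the arm, and the article describes no adjudication by the physician. The Discussion calls the trial open, acknowledges possible bias from the lack of double-blinding, and treats work absence as objective. This limits the likely effect but does not remove the conflict, because Randomization relies on the physician's blind and the motive still passes through that physician.

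A third reply is that a wider route exists: the Control group section has these same physicians collect the treatment each participant follows, at follow-up visits too. That reaches the whole sample and matters more. It is a separate issue and does not cancel this one.

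It is also tempting to argue that the interview re-exposes one arm to the program in mid-follow-up. That adds little. Intervention participants are already told to exercise daily at home, receive program questionnaires at 6, 12 and 24 months after the program, and have their exercise execution assessed at 18 months.

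**Conclusion.** The point holds in a narrow form. An intervention-only interview is tied to the visit of the physician whose blind the protocol relies on, and that physician later learns the motives that decide second-year recurrences. About thirty people are concerned, 9.2% of one arm and no controls.

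Two broader readings are not supported. The schedule does not show the arm in general, since about 295 of 325 intervention participants have no interview either. Nor is half of the primary-outcome data at risk: half of the follow-up time remains at 12 months, but recurrences recorded by then are fixed.

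The possible effect is small: at most about 0.9 to 1.6 points in the intervention arm's rate, against a planned 11.25. This assumes the planned 33.75% rate, 30 to 50% of first recurrences in year 2, and misattribution of every one of those among interviewees. An effect of this size would be unlikely to reverse the result by itself. The priority is low, and the change is worth making because it is cheap and protects a safeguard that the protocol itself sets.

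**What to change.** **Interviews still to be held.** Separate them from the occupational physician's visit, either by telephone or on another day, arranged by the data coordinating center without the occupational health service. Alternatively, hold them after that participant's 24-month visit. The cost is one extra contact for about thirty people, or longer recall if the interview moves past 24 months.

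**Interviews already held.** Follow-up visits describes them in the past tense, so rescheduling may come too late for some or all. Report whether the physicians were aware of them and how they were arranged. As a supportive check only, compare first-year recurrences between the arms in all participants, with the same rule in both. This uses data recorded before any interview. It answers a one-year question and loses the year-2 events, 30 to 50% of first recurrences under the assumption above, so power falls and it cannot replace the primary analysis.

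The check should not drop post-interview recurrences from interviewees alone. The cut-off would be undefined for controls and for intervention participants without an interview, and removing events from one arm would favor the program.

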### Analysis

Data analysis will be carried out with SAS® statistical analysis software (Version 9.2, SAS Institute Inc., Cary, USA). Results will be expressed with their 95% confidence intervals. All statistical tests were two sided p-value less than 0.05 regarded as significant. An intention-to-treat analysis will first be performed on all of the participants. This analysis may be supplemented with a per-protocol analysis involving the participants for whom the follow-up adhered to the protocol, therefore excluding all deviations from the protocol (see above Table
1).

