### Number of subjects required

With a recurrence rate estimated at 45% for the general population, in order to observe a 25% reduction in recurrence rate that is attributable to the global secondary prevention program, 310 participants per group (a total of 620 participants) are required to achieve at 80% power with Type 1 error rate of 5%.

A 5% increase in the number of participants is planned in order to take into account those lost to follow-up who do not attend all appointments, as well as any early dropouts. The total number of subjects is therefore set at 650.

These 650 professionals were recruited from within ten occupational health services belonging to the participating hospital facilities.

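### Table 1 removes participants with a missing primary outcome from the analysis, which contradicts the promised intention-to-treat analysis of all participants

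*Protocol article*

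**What the plan says.** The Analysis section sets the main analysis: "An intention-to-treat analysis will first be performed on all of the participants". A per-protocol analysis may follow, and the section refers to Table 1 for the deviations it would exclude.

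Two rows of Table 1 (Management of protocol violations) bear on missing outcomes. Row 3 deals with missed visits. It prescribes reminders by mail and then by telephone, and gives the reason: "It is important to have access to main criterion data for all participants in order to proceed to intention-to-treat analysis". Row 5 deals with a missing primary outcome: "These participants cannot be taken into account in the analysis of data".

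The primary outcome is at least one recurrence over two years, where a recurrence is a new low back pain episode that results in sick leave. Under Follow-up visits, the occupational physicians "have access to the date and duration of the work interruptions declared for each participant and can learn the motives from the participant", the latter at the annual checkups. The article concludes that collection will be comprehensive, yet the sample size section adds 5% for losses and dropouts.

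**The concern.** Row 5 is a complete-case rule for the primary outcome. It is stated without restriction to the per-protocol set, so it contradicts the intention-to-treat commitment. This is a rule that the article fixes, not a detail it leaves open.

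The described data flow suggests who might be deleted. A participant with no leave on record can be classified without attending. A participant with a recorded leave who does not give the reason cannot. Leave is a necessary part of the event, so that second group should contain more recurrences than the trial as a whole, although some of its leaves will have other causes. Deleting it would lower the observed recurrence rate in both arms. If deletion were also unequal between arms, the treatment contrast would be biased. Participants know their group, so unequal loss is possible.

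**Working it through.** **Inputs from the protocol article.** Control rate 45%; 25% reduction; 310 per group; 80% power; two-sided 5% level; 5% allowance; 650 in total (325 per group); chi-squared test of proportions. The share with a missing outcome is not given, so every share below is an assumption.

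**1. The plan's own figure.** A relative reduction gives 0.45 × 0.75 = 0.3375, a difference of 11.25 points. (A 25-point absolute reduction would need only 54 to 62 per group, so relative is meant.) The usual two-proportion formula gives 295 per group, or 313 with continuity correction. The stated 310 is reproduced by the corrected version. 620 × 1.05 = 651, close to the stated 650.

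**2. Power after deletion** (uncorrected formula, equal loss in both arms):

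| Deleted per arm | Analysed per arm | Power |
|---|---|---|
| 0% | 325 | 0.837 |
| 5% | 308.75 | 0.818 |
| 10% | 292.5 | 0.797 |
| 20% | 260 | 0.749 |

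At the planned 5% loss, power stays above 80%. Power is not the issue.

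**3. How far the result for all randomised participants could move.** Let a share m be missing in each arm and let completers show 45% versus 33.75%. The full-sample difference is (1 − m) × 11.25 + m × d, where d is the control-minus-intervention difference among the missing, from −100 to +100 points.
- m = 5%: 10.69 ± 5, or 5.7 to 15.7 points.
- m = 10%: 10.125 ± 10, or 0.1 to 20.1 points.

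With m = 5%, the complete-case result has z of about 2.86 (p about 0.004). At the unfavourable extreme the rates are 0.45 × 0.95 = 42.75% and 0.3375 × 0.95 + 0.05 = 37.06%. With 325 per group, z is about 1.48 and p about 0.14. The extremes require every missing participant in one arm to have recurred and none in the other.

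**4. Loss confined to recurrences.** If a share m of recurrences is deleted and no one else, the observed rate is p(1 − m)/(1 − pm).

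| Deleted, control / intervention | Observed rates | Risk ratio (true 0.75) |
|---|---|---|
| 10% / 10% | 42.4% / 31.4% | 0.741 |
| 20% / 20% | 39.6% / 29.0% | 0.732 |
| 20% / 10% | 39.6% / 31.4% | 0.795 |
| 10% / 20% | 42.4% / 29.0% | 0.683 |

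Equal loss lowers both rates and barely changes the ratio. Unequal loss moves the ratio in either direction.

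**The case against.** The best defence is that row 5 is only loosely worded. Table 1 lists protocol violations, the Analysis section cites it only for per-protocol exclusions, and row 3 ties intention-to-treat to having the outcome. On that reading the plan means intention-to-treat among participants with available outcomes, with sensitivity analyses left to a fuller document. This is a possible intention, but row 5 bars these participants from the analysis of data in general. Even on the narrow reading, the promise to analyse everyone would need rewording.

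Other parts of the defence do stand, and they rule out stronger readings:

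- **That missing outcomes are caused by leaves of unknown reason.** This is an inference from the data flow, and no sentence in the article says it. Early withdrawal is another route, and leaving the employer may be a third.
- **That row 5 deletes known outcomes.** It applies when the outcome is missing, not when a visit is missed; row 3 covers missed visits and deletes no one. A participant with no leave on record, or with a recurrence confirmed at 12 months, has a known outcome. The weakness is only that the article does not say so.
- **That the comparison is biased.** The physicians who collect the reasons are not told the allocation, and the reminders are not tied to arm. Unequal loss is not shown.
- **That the false-positive rate is inflated to some definite level.** With no true effect (45% in both arms), deleting 20% of recurrences in one arm and 5% in the other, from 310 per arm, gives 17.6% rejection. That assumes unequal loss and that no non-recurrent participant is deleted. If 25% of the non-recurrent also had leaves subject to the same unknown-reason rates, rejection falls to about 12%; at 50%, to about 8%.

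**Conclusion.** The contradiction between Table 1, row 5, and the Analysis section is established from the text and concerns the primary comparison. Deletion of leaves of unknown reason would understate recurrence in both arms. Distortion of the treatment contrast is a risk that depends on unequal loss, and the article gives neither its direction nor its size. With an assumed 5% missing per arm and completers at the planned rates, the result for all randomised participants could lie anywhere from 5.7 to 15.7 points. That is an outer limit and not an expected error, but its lower end would no longer be significant. A reader should not infer that the trial's result is biased or that its power is inadequate.

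**What to change.** Replace row 5 and align it with the Analysis section:

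1. Every randomised participant stays in the primary analysis.
2. Outcomes are classified from the leave records, where consent allows. No recorded leave over the 24 months counts as no recurrence. Any confirmed low back pain leave counts as a recurrence, even if later data are missing.
3. One rule, stated in advance, covers participants whose outcome remains unknown, such as a leave of unknown reason or records that stop early.
4. Two sensitivity analyses bound that rule: all unknown outcomes counted as recurrences, and none counted.
5. The chi-squared comparison remains the primary test.

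If the two analyses in item 4 treat both arms alike, they differ from each other only when the missing share differs by arm. With 5% missing in each arm, both give 47.75 − 37.06 = 42.75 − 32.06 = 10.7 points. The 5.7 to 15.7 range comes from opposite assumptions in the two arms and can be reported beside them.

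The cost is revised wording, a little more programming and an explicit assumption about unknown reasons. By the article's account the physicians already have access to the leave records. Whether these may be used after withdrawal depends on consent terms that are not shown.
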